## Abstract

**Background:** There is an urgent need to protect children against dengue since this age group is particularly sensitive to the disease. Since dengue vectors are active mainly during the day, a potential target for control should be schools where children spend a considerable amount of their day. School uniforms are the cultural norm in most developing countries, worn throughout the day. We hypothesise that insecticide-treated school uniforms will reduce the incidence of dengue infection in school-aged children. Our objective is to determine the impact of impregnated school uniforms on dengue incidence.

**Methods:** A randomised controlled trial will be conducted in eastern Thailand in a group of schools with approximately 2,000 students aged 7–18 years. Pre-fabricated school uniforms will be commercially treated to ensure consistent, high-quality insecticide impregnation with permethrin. A double-blind, randomised, crossover trial at the school level will cover two dengue transmission seasons.

**Discussion:** Practical issues and plans concerning intervention implementation, evaluation, analysing and interpreting the data, and possible policy implications arising from the trial are discussed.

**Trial registration:** clinicaltrial.gov. Registration number: NCT01563640

**Keywords:** Dengue, Insecticide-treated clothes, School children, School uniforms, Randomised control trial, Cost effectiveness

## Background

Dengue viruses are among the most geographically widespread of the arboviruses and are found in tropical and subtropical areas, where 2.5–3 billion people are at risk of infection [1]. Each year an estimated 230 million dengue infections occur; these infections result in over 2 million cases of dengue haemorrhagic fever (DHF) and about 20,000 deaths [1–3]. Globally, the number of disability-adjusted life years (DALYs) lost to dengue is estimated to range between 528 and 621 per million

population, a significantly high number that warrants enhanced control strategies [4]. The World Health Organisation (WHO) states that the Southeast Asian and Western Pacific regions bear nearly 75% of the current global disease burden of dengue [4]. Thailand is one of the countries with the highest dengue incidence [5].

Children carry the main burden of morbidity and mortality for dengue with a higher rate of complications, including DHF and shock syndromes, than in adults [6]. Infection in children causes disruptions in schooling and parental wage earning, which in turn have major direct effects on nutrition and overall family health. It is estimated that dengue contributes 465.3 DALYs per million population per year among school-aged children in

\* Correspondence: [contact]

Center of Excellence for Vectors and Vector-Borne Diseases, Faculty of Science, Mahidol University at Salaya, Nakhon Phatom, Thailand  
Full list of author information is available at the end of the article

northern Thailand, which accounts for 15% of all DALYs lost from febrile illness in this age group [7].

Past dengue control efforts have generally focussed on vector control but have been largely ineffective [4]. There is an urgent need for integrated and complementary population-based strategies to protect vulnerable children. The dengue vectors, *Aedes aegypti* and *Ae. albopictus*, are active mainly during the day when children are at school. Therefore, schools are potentially a key target for control. School uniforms are a cultural norm in most developing countries and are worn throughout the day on an almost daily basis.

Insecticide-treated fabrics have emerged as a key component of malaria disease control efforts following the widespread increased use of long-lasting insecticidal nets (LLINs) in recent years [8]. However, LLINs are likely to be relatively ineffective for dengue control since transmission occurs during the day when people are outside the protection of their nets. There have been a considerable number of strategies that have applied insecticide to personal clothing, but the application has been limited to military and recreational markets and has not reached community-based protection [9,10].

The most common insecticide applied to clothing is permethrin, a pyrethroid, which has an excellent safety record [11,12]. Permethrin is registered with the US Environmental Protection Agency (EPA) and approved by WHO for use in fabrics and clothing. Although the insecticide will transfer from the fabric to the skin, there is little evidence of adverse effects, and when used at appropriate concentrations, insecticide-treated clothing is deemed safe [13].

Commercially available fabrics made from a proprietary permethrin formula bound tightly to fabric fibres result in an effective, odourless protection against many biting arthropods including *Anopheles*, *Culex* and *Aedes* mosquitoes [14-16], ticks [17,18], chigger mites [19,20], and body lice [15]. Studies have shown that wearing permethrin-treated clothing led to reduced biting rates of *Aedes* mosquitoes by >90% in the areas covered by the clothing [21]. Although permethrin-treated clothing is used predominantly in recreational markets and the military, some studies have demonstrated that it can impact disease transmission [22]. For example, a randomised controlled trial of Colombian soldiers found that wearing permethrin-impregnated uniforms significantly reduced the incidence of malaria and cutaneous leishmaniasis by 75% compared with wearing non-impregnated uniforms [10]. The potential of using impregnated clothing and bedding has been shown in Pakistan [23] and Kenya [24] for malaria control. Tests have also shown that factory-based dipping methods of impregnating clothing can retain an effective repellence and knockout effect after 70 washings [25].

We aim to test our hypothesis [26] that insecticide-treated school uniforms will reduce the incidence of dengue in school-aged children. We will conduct a community-based randomised controlled trial in Thailand. This trial is conducted by partners of research area 2 in the "DengueTools" consortium [27].

## Study objectives

### Primary objective

The primary objective is to assess the impact of impregnated pre-fabricated school uniforms on laboratory-confirmed dengue incidence in school-aged children.

### Secondary objectives

#### Clinical

- To assess the impact of impregnated school uniforms on the number of febrile episodes during the study period (compared to the control group)
- To assess the impact of impregnated school uniforms on school absenteeism (number of days lost because of febrile illness)
- To measure the protective herd effect (halo effect) on dengue incidence in children without impregnated clothes
- To assess the safety of impregnated school uniforms in children

#### Entomological and ecological

- To investigate the effect of impregnated school uniforms on vector abundance in and around schools
- To determine whether impregnated clothing affects behaviours associated with adult mosquito feeding and indoor resting
- To determine the environmental and socioeconomic risk factors associated with dengue infections

#### Economic analysis

- To estimate the costs of dengue infection in school-aged children
- To estimate the costs and cost-effectiveness of impregnated school uniforms for the prevention of dengue in school-aged children

#### Social science

- To assess the behaviour of Thai school-aged children with regard to wearing the school uniform and washing practices of school uniforms
- To assess the perception of dengue severity in the community (school teachers and parents)

- To assess the acceptability of impregnated school uniforms in children
- To assess community acceptance of impregnated school uniforms and the trial

## Methods/Design

### Study area and participant eligibility

The study area is located about 150 km east of Bangkok at transmission foci in Plaeng Yao District, Chachoengsao Province, eastern Thailand. Our Thai research group has already established excellent relationships with local schools because of a decade of research in this area [28–30]. The climate consists of a rainy season from May to October followed by a long dry season. The region covers an area of 237 km^2 and a population of 36,607 persons (census 2005; [http://en.wikipedia.org/wiki/Plaeng\\_Yao\\_District](http://en.wikipedia.org/wiki/Plaeng_Yao_District)). There are 24 primary and secondary schools in this area, of which we will select 10 schools that have between 100–500 students who are willing to participate. All children aged 7 to 18 years old will be eligible. In order for the results from this study to be as generalisable as possible, with the exception of children with eczema or other severe underlying skin diseases, no exclusions will be made on the basis of gender, ethnic group, medical condition or physical health. Inclusion will require parents/caretakers to give informed written consent; in the case of children older than 12 years, assent will also be required. Subjects and households will be free to withdraw from participating in the study at any time without giving a reason. To ensure a high compliance rate among children in participating schools, awareness campaigns in the community and in the schools will be held. Information sessions with the school leadership, school teachers and parents will be conducted between October 2011 and May 2012 before the start of trial.

Study subjects will be enrolled between January and June 2012. The intervention/control will commence in mid-May to June 2012, at the start of the Thai school year.

### Intervention

Routinely used school uniforms will be collected from all consenting children and treated with a long-lasting permethrin formulation, using a factory proprietary method. The process involves coating the uniforms in a proprietary formula containing 0.52% permethrin (Insect Shield USEPA2009). The technology claims to provide 80–96.7% knockdown after 70 washes [25]. Enrolled children will receive either permethrin impregnated or untreated school uniforms. For schools assigned to the control group, uniforms will be collected and washed using the same methodology as those used in the

treatment group, but without the impregnation process with permethrin.

School uniforms vary in form, colour and size. School uniforms include the regular school uniform, scouts uniform, sports uniform and cultural uniform. Most of the typical uniforms are short-sleeved and only cover the legs down to the knees (shorts or skirts). The variation between the schools is minimal for the uniforms, except for the cultural uniform.

### Design

A cluster-randomised, double-blinded, crossover design will be implemented. Randomisation will be by school. An individual participation rate of at least 90% within each school is anticipated. The schools will be randomised into two equal groups, with each school receiving impregnated uniforms in either the first (2012–13) or second (2013–14) annual transmission season covered by the trial.

### Randomisation and blinding

There will be double-blinding: neither the children nor the investigators will know the allocation. School uniforms from Thailand will be sent to the InsectShield factory: one group will undergo washing and treatment with permethrin. The control group will only undergo washing. Both the impregnated and washed uniforms will be identified with labels indicating the child's name, school and year, but there will be no identifiable indication as to which uniforms are actually impregnated.

All participating schools will be stratified into two by enrolment size, above and below median. Randomisation to two groups (intervention followed by control, control followed by intervention) will be carried out in Sweden. This information will be kept confidential between one epidemiologist and the impregnation facility.

### Sample size

Sample size for the trial will take into account likely levels of dengue incidence, as well as the considerable wide-area variation in transmission from season to season, and local area (i.e., per school) variation [31]. Such large potential variations are unpredictable and difficult to quantify. The advantage of the crossover school-randomised design – which can be interpreted as a cluster-randomised design in relation to individuals – is that if there are particular factors driving local area variation from year to year (such as mosquito breeding sites close to schools), those sources of variation will, to some extent, be controlled by the crossover design. This design efficiency is a considerable advantage, notwithstanding the relatively large design effect that needs to be

applied to the overall sample size in recognition of the cluster randomisation and the considerable uncertainties around wide-area incidence rates from year to year.

In view of the probable large size of these variations and their inherent uncertainty, a design factor of 3 is used.

A design factor greater than unity is justified because of the school clustering effect. Unfortunately, because of the paucity of knowledge of dengue epidemiology, both in terms of year-on-year variation and its determinants in Thailand in general, and compounded by possible local variations in dengue that might occur between school locations, it is impossible to make detailed calculations of the required design effect. The choice of 3 as the design effect was therefore adopted as a conservative estimate in the absence of being able to make any better estimate.

The basic assumptions underlying the sample size for the trial are an incidence rate (symptomatic plus asymptomatic) of an average of 5% during a transmission season [32], i.e. 10% over two seasons; an aim of halving incidence by using impregnated uniforms (since any smaller effect would not be of policy interest) and a dropout rate (children leaving the school, etc.) of 20%.

According to Schouten and Kester [33], the overall sample size for a non-clustered crossover design can be calculated as

$$2n = \frac{[z_1 - \alpha/2\sqrt{\pi_A(1 - \pi_B) + \pi_B(1 - \pi_A)} + z_1 - \beta\sqrt{\pi_A(1 - \pi_A) + \pi_B(1 - \pi_B)}]^2}{(\pi_A - \pi_B)^2}$$

For comparing a 10% incidence with 5%, this amounts to an overall sample size of 508 (90% power,  $p = 0.05$ ). Increasing this figure by 20% to allow for dropout takes this to 610, and allowing for 10% of children to become infected and take no further part in the trial takes this to 670. A design effect of 3 then takes the total sample size to 2,012 (i.e., 1,006 in each study arm).

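### The sample size enters two-season risks (10% vs 5%) into a crossover formula although each condition lasts one season; on the plan's own assumptions the inputs are 5% vs 2.5%, and 2,012 children give about 55% power for a halving at the assumed design effect of 3

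*Protocol*

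**What the plan says.** The Sample size section of the protocol assumes "an incidence rate (symptomatic plus asymptomatic) of an average of 5% during a transmission season [32], i.e. 10% over two seasons" and gives the target as "an aim of halving incidence by using impregnated uniforms (since any smaller effect would not be of policy interest". It prints a formula, introduced with the words "the overall sample size for a non-clustered crossover design can be calculated as", whose inputs are a risk under each of two conditions, A and B. The result is reported as "For comparing a 10% incidence with 5%, this amounts to an overall sample size of 508", at 90% power and a significance level of 0.05. Inflation follows: "Increasing this figure by 20% to allow for dropout takes this to 610", then a further 10% for infected children who leave the trial (670), then a design effect of 3, ending at 2,012.

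The Design section has "each school receiving impregnated uniforms in either the first (2012–13) or second (2013–14) annual transmission season covered by the trial". The Randomisation and blinding section confirms two sequences: "Randomisation to two groups (intervention followed by control, control followed by intervention".

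**The concern.** In a two-period crossover, each of the formula's two risks is one child's risk during the period spent in that condition. Here a period is one transmission season. The protocol's own assumption is 5% per untreated season, so a halving means 2.5% in the treated season. The 10% is the risk over two untreated seasons, which no child following the schedule experiences. Entering 10% and 5% would require two seasons in each condition, and nothing in the protocol provides for that. The entry doubles the expected events in each period.

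The protocol treats a halving as the smallest effect of policy interest. If power for that effect is well below 90%, a non-significant result says much less than the protocol implies. The Discussion lists reasons for a null result (wearing time, exposure after school, loss of effect through washing) and does not include limited power.

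**Working it through.** **Inputs from the protocol.** Untreated risk per season 5%; effect a halving; power 90%; alpha 0.05, two-sided because the formula uses the 1 − α/2 quantile; inflation factors 1.2 (dropout), 1.1 (infected children leaving) and 3 (design effect).

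**Formula as printed.** N = 2n = [1.960·a + 1.2816·b]² / (πA − πB)², where a = √[πA(1 − πB) + πB(1 − πA)] and b = √[πA(1 − πA) + πB(1 − πB)].
Solved for power: Φ{[√N·(πA − πB) − 1.960·a] / b}.

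**Step 1: the plan's own figure (10% vs 5%).**
- a = √0.14 = 0.3742; b = √0.1375 = 0.3708.
- N = (0.7334 + 0.4752)² / 0.0025 = 584.3. The protocol states 508.
- A one-sided test gives 476 and 85% power gives 500, so neither explains 508.
- Power of 508 for 10% vs 5%: Φ[(√508 × 0.05 − 0.7334) / 0.3708] = Φ(1.061) = 85.6%.
- The inflation chain itself reproduces: 508 × 1.2 × 1.1 × 3 = 2,011.7, i.e. 2,012.

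**Step 2: per-season risks (5% vs 2.5%).**
- a = √0.0725 = 0.2693; b = √0.071875 = 0.2681.
- N = (0.5277 + 0.3436)² / 0.000625 = 1,214.7, i.e. 1,215. The like-for-like ratio is 1,215 / 584 = 2.1.
- Inflated as stated: 1,214.7 × 1.2 × 1.1 × 3 ≈ 4,810.
- With the loss to infection cut to one untreated season (5%): 1,214.7 × 1.2 × 1.05 × 3 ≈ 4,590.

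**Step 3: power of the planned 2,012 for a halving.** The effective number is 2,012 / (1.2 × 1.1 × 3) = 508.
- Power = Φ[(√508 × 0.025 − 0.5277) / 0.2681] = Φ(0.133) = 55.3%.
- From a base of 584 instead of 508: Φ[(√584 × 0.025 − 0.5277) / 0.2681] = Φ(0.285) = 61%.
- Detectable effect with 508: solving for 90% power gives a treated risk of 1.4%, a reduction of about 72%.

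**Step 4: sensitivity of the power for 5% vs 2.5% with 2,012 enrolled.**

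| Assumption | Power |
|---|---|
| Design effect 3, losses as stated | 55% |
| Design effect 3, losses taken as ×0.8 ×0.9 | 53% |
| Design effect 3, infection allowance 5% | 57% |
| Design effect 3, no losses | 67% |
| Design effect 2, losses as stated | 73% |
| Design effect 1.5, losses as stated | 84% |
| Design effect 1, losses as stated | 95% |

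**The case against.** The best defence of the 10% is that the trial runs for two seasons, so a two-season incidence is the natural input. That fails for a crossover formula, which already uses both periods of every child. Putting two-season risks into it counts the second season twice.

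The stronger defence concerns the size of the shortfall. The protocol says the design effect cannot be calculated in detail, calls 3 conservative, and expects the crossover to absorb some local variation. With a smaller true design effect the power would be higher, as the table shows; it reaches 90% at about 1.25. This stands. The 55% tests the plan against its own assumption and is not an unconditional property of the trial.

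Three stronger readings are tempting and are not supported.
- A reader might attribute the whole fall from 90% to 55% to the season mismatch. Part of it belongs to the separate discrepancy between 508 and 584. The mismatch alone accounts for 86% to 55%, or 90% to 61% from a base of 584.
- A reader might quote 4,810 as the single corrected total. It retains a 10% infection allowance equal to the two-season untreated incidence; the one-season figure gives about 4,590.
- A reader might lower the power further by assuming a school-level t-test on the few degrees of freedom that ten schools allow. The protocol specifies no such test. Its Analytical plan speaks only of incidence rates per person-time, and the details may lie in an analysis plan not at hand.

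**Conclusion.** The point holds. The 90% power claimed for halving incidence does not follow from the protocol's assumptions, because the formula's inputs cover two seasons and each condition lasts one. On the printed formula the uninflated requirement is 1,215 children rather than 584, and the inflated total is about 4,590 to 4,810 rather than 2,012. At the plan's design effect of 3, the planned 2,012 give about 55% power for a halving and 90% only for about a 72% reduction.

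This rests on the 5% per-season incidence, the printed formula, a two-sided 0.05 level and the stated loss factors. The conclusion that power is below 90% survives every variant tried except a design effect of 1.25 or less. The protocol argues for a value above 1 and adopts 3.

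**What to change.** In the Sample size section of the protocol:
- Replace 10% and 5% by the per-season risks, 5% and 2.5%, and state that each formula input refers to one season.
- Correct the 508: the printed formula gives 584 for 10% vs 5% and 1,215 for 5% vs 2.5%.
- Restate the power of 2,012 children as about 55% for a halving, conditional on the design effect of 3, with the detectable reduction (about 72%) and the power at smaller design effects (73% at 2, 84% at 1.5).
- Align the allowance for infected children with the same one-season incidence, or explain why 10% is kept.
- Alternatively, if 10% per season is what is believed, say so, justify it from the incidence source, and still correct the 508.

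The cost is a recalculation and revised wording. No change in enrolment is needed to make the statement correct; the downside is a less favourable stated power.

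### The printed crossover formula with the stated inputs gives 585 children, not 508, so the stated 90% power is overstated: 2,012 children give about 84–87% for 10% vs 5% at the assumed design effect of 3

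*Protocol*

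**What the plan says.** The Sample size section of the Protocol takes a formula from a cited methods paper and introduces it with the words "the overall sample size for a non-clustered crossover design can be calculated as". The formula puts the normal quantile at 1 − α/2 on the first term, so the test is two-sided.

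The assumptions are an incidence "of an average of 5% during a transmission season [32], i.e. 10% over two seasons", and "an aim of halving incidence by using impregnated uniforms". The result is then given: "For comparing a 10% incidence with 5%, this amounts to an overall sample size of 508", with 90% power and p = 0.05.

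The inflation follows in three steps. The first is "Increasing this figure by 20% to allow for dropout takes this to 610". The second allows for 10% of children being infected and leaving the trial, which gives 670. The third applies a design effect of 3, which gives 2,012 in total or 1,006 per arm.

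**The concern.** Formula, inputs and answer are all printed in one section, and the answer does not follow from the other two. This is not a detail left for a later analysis plan. The total of 2,012 and the 90% power both rest on the base figure, and the design effect multiplies any error in it by three.

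The allowance for dropout has a smaller problem of its own. Raising a number by 20% and then losing 20% does not return the starting number.

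What is at stake is the power the trial claims. The Discussion commits the investigators to explaining a null result by reasons such as wearing time or washing. If power is overstated, chance failure to detect a real effect will be given too little weight among those reasons.

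**Working it through.** **Inputs** (all from the Protocol, Sample size): π_A = 0.10, π_B = 0.05, two-sided α = 0.05 (z = 1.95996), power 90% (z = 1.28155), dropout 20%, loss through infection 10%, design effect 3.

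**1. The plan's chain from 508.**
- 508 × 1.2 = 609.6
- 609.6 × 1.1 = 670.56
- 670.56 × 3 = 2,011.7

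This reproduces 610, 670 and 2,012. The inflation is therefore multiplication by 1 + loss at each step, and the chain is consistent once 508 is accepted.

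**2. The base figure.** The formula is

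2n = [z(1−α/2)·√(π_A(1−π_B) + π_B(1−π_A)) + z(1−β)·√(π_A(1−π_A) + π_B(1−π_B))]² / (π_A − π_B)²

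- First variance term: 0.10 × 0.95 + 0.05 × 0.90 = 0.14; 1.95996 × √0.14 = 0.7334
- Second variance term: 0.10 × 0.90 + 0.05 × 0.95 = 0.1375; 1.28155 × √0.1375 = 0.4752
- Sum 1.2086; squared and divided by 0.05² = 0.0025: 584.25, so **585**

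585 is 15% above 508. The second variance term equals the first minus (π_A − π_B)², 0.14 − 0.0025 = 0.1375, so the formula is coherent as printed and damaged typesetting does not explain the gap.

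**3. Other settings of the same formula.**

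| Setting | 2n |
|---|---|
| Two-sided 5%, 90% power (as stated) | 584.25 |
| Two-sided 5%, 85% power | 499.7 |
| Two-sided 5%, 80% power | 437.2 |
| One-sided 5%, 90% power | 475.8 |

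The nearest is 85% power, which contradicts the stated 90%. A within-child correlation of about 0.14 would also give about 508, but the formula has no such term and the Protocol states no correlation.

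**4. Power at a given number N of evaluable children.** Solving the formula for power:

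power = Φ[(√N × 0.05 − 1.95996 × √0.14) / √0.1375]

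At N = 508: (1.1269 − 0.7334)/0.3708 = 1.061, so power is **85.6%**. At N = 585 it is 90.0%.

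**5. The dropout step.** To keep 508 after losing 20%, 508/0.80 = 635 are needed, not 610. The 610 (609.6) leave 609.6 × 0.80 = 487.7.

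**6. Power of 2,012 children at design effect 3.** 2,012/3 = 670.7 before losses.

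| Loss assumption | Evaluable | Power, 10% vs 5% |
|---|---|---|
| 20% and 10%, both total losses | 670.7 × 0.8 × 0.9 = 482.9 | 83.8% |
| The plan's own chain | 508 | 85.6% |
| 20%, and 3.75% infected in season 1 | 670.7 × 0.8 × 0.9625 = 516.4 | 86.1% |
| 20% only | 670.7 × 0.8 = 536.5 | 87.4% |

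The 3.75% is the mean of 5% in schools that start as control and 2.5% in schools that start treated. It uses the plan's 5% per season and halving.

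**7. Corrected totals.**
- Plan's own multipliers: 585 × 1.2 × 1.1 × 3 = 2,316.6, so 2,317
- Dropout divided out, 10% step as in the plan: 585/0.8 × 1.1 × 3 = 2,413.1, so 2,414
- Both losses divided out: 585/(0.8 × 0.9) × 3 = 2,437.5, so 2,438

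**The case against.** **The infected children are not lost.** Under the Analytical plan the primary endpoint counts person-time up to dengue infection or censoring, so an infected child contributes an event and time at risk. The 10% is also the two-season control figure, and only children infected in season 1 miss season 2. In addition, Safety considerations provides for replacing children who leave in year 1. This stands. A reader might infer that both losses must be divided out, that 2,438 is therefore the correct total, and that 84% is the power of the trial. The documents do not support that. Dividing by 0.90 treats endpoint events as if they carried no information, and 84% is only the low end of the range. What the objection cannot rescue is the base figure, since 508 fully evaluable children still give 85.6%.

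**The design effect dominates.** The Protocol says openly that 3 is a conservative choice made because no detailed calculation was possible. Even with both losses counted as total, 2,012 children reach 90% at a design effect of 2.48. On the same basis power is 95% at 2 and 72% at 4. This also stands: every power figure here is conditional on 3, and the 15% slip is smaller than that uncertainty. But a factor chosen to cover clustering cannot also be counted on to absorb an arithmetic error.

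**The incidence inputs.** A reader might add that one season of each treatment implies 5% vs 2.5%, where the same formula gives about 53% power if both losses are total. That is a separate question about which rates to enter, and it adds nothing to the present point, which takes 10% vs 5% as stated.

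**Conclusion.** The sample size is wrong as written. The printed formula with the stated inputs gives 585, not 508, and 508 evaluable children give 85.6% power. This needs no assumption beyond the Protocol's own text.

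Applying the dropout as ×1.2 where ÷0.80 is needed is a secondary error. The 10% step is not shown to be wrong, but it is unexplained given the endpoint definition.

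For the planned 2,012 children, power for 10% vs 5% is about 84–87%, below the stated 90% in every loss scenario examined. The shortfall is about 3 to 6 percentage points. That range takes the design effect of 3 as given and gives no credit for replacement of children who leave in year 1.

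**What to change.** 1. Replace 508 by 585 in the Sample size section. If 508 came from a different setting or from an assumed within-child correlation, state that setting and the formula that includes it.
2. Apply the 20% dropout by division by 0.80.
3. Justify the 10% step for infected children against the person-time endpoint in the Analytical plan and the replacement rule in Safety considerations. Do not simply exchange ×1.1 for ÷0.90.
4. Carry the figures through: 2,317 with the plan's own multipliers, 2,414 with only the dropout divided out, up to 2,438 with both divided out. If step 3 concludes that no allowance for infection is needed, the total is 585/0.8 × 3 = 2,193.75, so 2,194.
5. If 2,012 is kept, replace the stated 90% by about 84–87% for 10% vs 5%, and say that this is conditional on a design effect of 3.

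Keeping 2,012 costs only recalculation, rewording and a less favourable stated power. Keeping 90% power means enrolling 305 more children on the plan's own multipliers (2,317 − 2,012), up to 426 more with both losses divided out (2,438 − 2,012).
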